## Abstract

**Background:**

Noncommunicable diseases (NCDs) are increasingly becoming a public health challenge, particularly in resource-limited settings, due to limited access to preventive care, early detection, and health literacy. Nevertheless, there is immense potential for digital technologies to enhance the overall community health. Similarly, the World Health Organization (WHO) Package of Essential NCD (PEN) interventions for primary health care in low-resource settings has demonstrated evidence of improving NCD outcomes. Nevertheless, its effectiveness in the Indian setting has not been explored.

**Objective:**

This study aims to evaluate the effectiveness of a mobile and web-based digital intervention compared with the WHO PEN approach and a no-intervention control group in improving health-seeking behaviors, risk factor modification, and disease management related to NCD prevention and control in resource-limited settings across 4 Indian sites.

**Methods:**

A quasi-experimental, mixed methods study will be conducted across 4 sites in India by using cluster-based allocation. The study will be conducted in 3 phases, where the insights gathered in the first phase will guide the development of a human-centered digital health intervention to help people nudge toward better health-seeking behaviors for common NCDs (diabetes or hypertension/cardiovascular diseases or both). The effectiveness of the digital intervention will be compared against the WHO PEN intervention and a control group that will receive no intervention. Standard validation tools will be used to assess behavior and changes related to modifiable risk factors. Data will be analyzed using descriptive and inferential statistics, with pre-post comparisons and between-group analyses. Qualitative data will be thematically analyzed to complement quantitative findings.

**Results:**

The funding for this study was received from the Indian Council of Medical Research in January 2025. In phase 1, across all sites, a total of 80 in-depth interviews (community and community health workers), 320 Knowledge, Attitude, And Practice questionnaires (community), and 32 focus group discussions with 320 individuals (community) were conducted from July 2025 to December 2025. This will be followed by data analysis, and findings will be used to guide the development of the digital intervention. The results of this study are expected to be published in 2028. This study is expected to demonstrate improved health-seeking behavior, self-management practices, and lifestyle modifications among participants exposed to the digital intervention compared with the WHO PEN and control groups. Findings will illuminate the feasibility and scalability of integrating digital health solutions within community-based NCD prevention frameworks in India.

**Conclusions:**

This protocol outlines a community-based, multi-site comparative study to evaluate the role of digital health interventions vis-à-vis WHO PEN in addressing NCD prevention and management. The results will contribute to evidence-based recommendations for strengthening digital health integration in resource-limited primary care settings.

**International Registered Report Identifier (IRRID):**

DERR1-10.2196/89021

## Introduction

### Background

Globally, noncommunicable diseases (NCDs) such as heart disease, diabetes, chronic respiratory problems, and cancer account for over 70% of deaths annually. Nearly 80% of these deaths happen in low- and middle-income countries [1]. In India, these diseases cause about 63% of all deaths, and the identified risk factors, such as limited or no physical activity, poor dietary habits, obesity, tobacco use, and alcohol consumption, are increasingly adding to the overall burden [2,3]. Despite several attempts in India to enhance basic health care with programs like the National Program for the Prevention and Control of NCDs, issues such as failure in early detection, treatment adherence, and receiving continuous care are still persistent in resource-limited settings [4].

The World Health Organization’s Package of Essential NCD (WHO PEN) interventions was introduced as a cost-effective strategy to enable primary health care workers to deliver standardized NCD services in low-resource environments [5]. The major focus of the WHO PEN protocol is on task shifting, screening at the early stage, and risk-based management by using simple tools and strategies. This intervention has been effectively executed to improve the management of diabetes and hypertension at the community level [6]. However, there are several limitations such as inconsistent implementation, limited health worker training, and weak follow-up systems that interfere with the long-term impact in real-world contexts [7].

### Digital Health and Its Potential in NCD Management

Recent years have witnessed an influx of digital health interventions that include mobile apps, web-based platforms, teleconsultations, and data-driven dashboards as a promising strategy to enhance health care access and continuity [8]. The use of mobile technologies for NCD prevention and control can enhance health literacy, modification in health-seeking behaviors, and remote monitoring, especially in resource-constrained settings [9]. Digital interventions have demonstrated potential in improving medication adherence, promoting physical activity, and supporting lifestyle modification [10,11].

In the Indian scenario, digital health has amplified to a significant level under the Ayushman Bharat Digital Mission, the goal of which is to integrate digital tools into primary health care delivery [12]. Despite all the developments achieved over the years, there has been limited evidence on the comparative effectiveness of digital interventions versus standardized models such as WHO PEN, particularly in diverse community settings. Furthermore, identifying and understanding the barriers and facilitators to technology adoption and contextual dissimilarities across geographic and sociodemographic groups is critical for scaling such interventions.

### Rationale for the Study

There has been an increasing utilization and acceptance of digital health platforms. However, there is a scarcity of evidence that compares and evaluates the impact of digital interventions relative to the established WHO PEN based standard care. Most existing studies focus on single disease domains such as diabetes or hypertension rather than comprehensive NCD prevention frameworks [13]. Moreover, multisite evidence capturing both urban and semiurban populations is scarce in India.

This proposed study will focus on diabetes, hypertension, or cardiovascular diseases. Further, this study will address the gaps by focusing on behavioral modification and implementing and evaluating the digital intervention developed as part of this study and the behavioral component of WHO PEN as part of a multi-site, quasi-experimental design comparing 3 groups:

A digital intervention group: This group will be provided with a digital intervention platform that will comprise multilingual educational modules to enhance health literacy, self-management techniques, self-care tracking, and digital follow-up modules designed to empower individuals and facilitate continuous engagement.A WHO PEN group: This group will receive an intervention that would emphasize in-person screening, counselling, and follow-up based on established WHO guidelines.A control group: This group will receive no structured intervention beyond the routine care that they receive as part of their daily routine.

### Study Significance

This study will provide robust empirical evidence on the comparative effectiveness of digital and WHO PEN interventions in enhancing the overall health of the affected individuals by nudging them toward better health-seeking behaviors and self-management practices. Identifying and understanding the barriers and facilitators that influence the adoption of digital interventions in community settings will serve as the foundational guide for developing barriers to digital intervention. Additionally, it will provide enough insights to guide the policy integration of digital health solutions in India’s existing NCD prevention and control programs. The mixed methods approach across 4 diverse sites, namely, Delhi, Chennai, Sikkim, and Dehradun, is expected to capture variations in the demographic, cultural, and infrastructural contexts, thereby enhancing the generalizability of the findings. This study should help by strengthening further discussion on the improvement of digital health and creating successful disease management plans in places with limited resources.

### Objectives

The primary objectives are as follows:

Identify influential factors shaping healthy behavior and design a tailored model for NCD (diabetes and cardiovascular diseases) prevention and self-management, targeting the urban slums in India.Develop a personalized, human-centered, tailored, interactive, multilingual digital health intervention to enhance awareness of prevention and self-management of NCDs by using the findings of objective 1.Evaluate the feasibility of developing a digital health intervention for NCD prevention or self-management in urban slums of India comparing it to WHO PEN interventions for primary care.

The secondary objectives are as follows:

Assess the changes in knowledge, attitude, and practice scores related to NCD prevention across the 3 study groups.Identify contextual and sociodemographic factors that influence the adoption and sustained use of the digital platform, particularly in comparison to the implementation of WHO PEN.Generate implementation insights and policy recommendations for integrating digital tools within India’s existing NCD prevention and control programs.

## Methods

### Study Design and Setting

This is a multi-site, quasi-experimental study, using a cluster-design sampling strategy. This study adopts a mixed methods approach to assess the efficacy of using the WHO PEN in comparison with a control group that received no intervention and a digital intervention platform. The study is being conducted in urban poor settings in India across 4 sites with differing geographic and sociocultural characteristics. Allocation to study arms will occur at the community (cluster) level. Within each site, community clusters (wards/slum clusters) will be assigned to one of the 3 intervention arms to reduce contamination between participants and to align with local service delivery structures. All eligible individuals within a cluster are enrolled into the arm designated for that cluster.

The study will span 3 years and execute 3 distinct phases to achieve the 3 stated objectives. The interventions will be deployed in the third phase of the study and will include follow-up evaluations at 3 months, 6 months, 9 months, and 12 months post intervention.

### Inclusion and Exclusion Criteria

The individuals will be included if they are 18-70 years old, have diabetes or hypertension or cardiovascular diseases and/or both, can provide written informed consent, have access to a mobile phone (Android or any smartphone), and are willing to use technology. They will be excluded if they are younger than 18 years, have a terminal illness, have impaired cognition, are pregnant, fail to adhere to study procedures, or they are currently enrolled in another interventional study addressing the same outcomes.

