### Data Collection and Sampling Strategy

To ensure that each site implements all 3 arms while preserving feasibility and minimizing contamination, this study will use a clustered quasi-experimental design at the local community level.

#### Objective 1

To meet objective 1, both the quantitative and qualitative data will be collected. At each site, 8 focus group discussions will be conducted in community settings, with 8-10 individuals participating in each group. The in-depth interviews will be conducted with 10 individuals from the community and 10 community health workers. The Knowledge, Attitude, and Practice questionnaire, along with the other validated assessment tools, will be administered to 80 individuals from each site.

#### Objective 2

To meet objective 2, a total of 80 participants will be enrolled across 4 zones at each site to obtain their feedback on the developed digital platform.

#### Objective 3

To meet objective 3, participants at each site will be assigned to one of the following 3 study arms based on the site’s designated intervention:

Digital intervention arm: Participants will receive access to a mobile and web-based digital health platform developed by the Foundations of Healthcare Technologies Society, designed to promote NCD screening, health education, and behavior modification through interactive modules, personalized reminders, and self-tracking tools.WHO PEN arm: Participants will receive structured screening, counselling, and management services as per the WHO PEN protocols 1 and 2, implemented through trained health care providers and community health workers.Control arm: Participants will receive only routine health services available in their local setting, without any structured digital or WHO PEN-based intervention.

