### Strengths and Potential Limitations

A mixed methods approach will be utilized, integrating insights from behavioral, clinical, and qualitative measures to capture multidimensional outcomes. The human-centered design will ensure the digital intervention is tailored to the context of the target population, enhancing relevance and user engagement. The inclusion of geographically and culturally diverse sites such as Delhi (plains), Dehradun (valley), Chennai (coastal), and Sikkim (hilly) would provide an additional contextual understanding that would support external validity. Moreover, the incorporation of digital monitoring systems facilitates real-time data acquisition and guarantees the integrity of the interventions.

However, this study anticipates certain limitations. The nonrandomized allocation of participants may introduce selection bias, although cluster-based assignment and analytical adjustments will be employed to minimize its effects. Additionally, variations in digital literacy among participants may influence engagement with the intervention. Despite these constraints, the study is expected to yield robust insights into the differential effectiveness, user experience, and implementation feasibility of digital solutions for NCD prevention within the low- and middle-income country-setting contexts.

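### Listing failure to follow study procedures as an exclusion criterion allows people to be dropped after their arm is fixed, which can bias the arm comparison in a direction that is plausible but not certain

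*Protocol article*

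**What the plan says.** In Inclusion and Exclusion Criteria, people are excluded if they "fail to adhere to study procedures". The other items in that list, such as age, terminal illness, impaired cognition and pregnancy, can be checked at entry.

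Study Design and Setting assigns arms to community clusters and adds: "All eligible individuals within a cluster are enrolled into the arm designated for that cluster".

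Data Collection and Sampling Strategy (Objective 3) gives the arms different content:

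- Digital: "behavior modification through interactive modules, personalized reminders, and self-tracking tools".
- WHO PEN: "Participants will receive structured screening, counselling, and management services as per the WHO PEN protocols 1 and 2".
- Control: "Participants will receive only routine health services available in their local setting".

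The same section names health-seeking behaviour and NCD self-management as the primary outcomes. Strengths and Potential Limitations concedes that "The nonrandomized allocation of participants may introduce selection bias" and that "variations in digital literacy among participants may influence engagement with the intervention".

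The Data Analysis Plan handles missing data by maximum likelihood in a mixed model, with multiple imputation as a sensitivity analysis. The article does not say that non-adherent participants stay in follow-up or in the analysis.

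**The concern.** An eligibility rule should rest on facts known before enrolment. Whether someone follows study procedures is normally learned later, and here the arm is fixed before the person joins. A rule that removes such people therefore selects on behaviour that the arm itself may have influenced.

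Two features make this more than a matter of form. First, adherence is closely related to the primary outcomes: a person who ignores reminders or skips counselling is likely to score lower on self-management. Second, the arms differ in what there is to adhere to, so the share and kind of people removed can differ between them. If disengaged people leave mainly from an active arm, a more motivated remainder is compared with a less selected control group. The protocol already accepts selection bias from nonrandomized allocation. This rule would add a second source, and an avoidable one. It would also remove non-users, whom the secondary objective on adoption and sustained use of the platform needs.

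**Working it through.** **Does the text place the rule after allocation?** The cluster's arm is designated first and eligible people then enter it. No run-in is described, and the phrase is not limited to a judgement at screening. Willingness to use technology is already a separate inclusion criterion. Read literally, the rule acts after allocation.

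**Planned sample size.** Inputs from Data Collection and Sampling Strategy: 64 clusters, about 30 people each, intracluster correlation 0.02, design effect 1.58, d = 0.30, attrition 15% to 20%, total 2400.

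- Design effect: 1 + (30 − 1) × 0.02 = 1.58, as stated.
- Total: 64 × 30 = 1920; 1920 / (1 − 0.20) = 2400, as stated.
- Evaluable per arm, assuming an equal three-way split: 1920 / 3 = 640. Effective size: 640 / 1.58 = 405.

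**Illustration.** Assumptions, none from the documents: outcome SD 1, no true effect, no exclusions in control, and excluded people 0.3 SD worse than those retained. Exclusion shares of 10% and 20% are used. The upper share equals the top of the planned total attrition, and the exclusions are taken from the 640 evaluable.

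Bias = share excluded × outcome gap.

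- 10%: 0.10 × 0.3 = 0.03 SD; 0.03 / 0.30 = 10% of the planned effect.
- 20%: 0.20 × 0.3 = 0.06 SD; 0.06 / 0.30 = 20% of the planned effect.

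**Two-sided error at 20%, unadjusted 5% test, allowing for the smaller digital arm.**

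- Digital arm: 640 × 0.80 = 512 people in clusters of 24. Design effect: 1 + 23 × 0.02 = 1.46. Effective size: 512 / 1.46 = 351.
- SE = √(1/351 + 1/405) = 0.0729.
- Shift = 0.06 / 0.0729 = 0.82.
- P(Z > 1.96 − 0.82) + P(Z < −1.96 − 0.82) = about 0.13.

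The same steps at 10% (576 people, clusters of 27, design effect 1.52, effective size 379, SE 0.0715) give about 0.07.

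**Sensitivity to the model and to which arm loses people.** A second model, also assumed, excludes the least adherent share of an arm and lets latent adherence correlate with outcome at 0.2 to 0.5. Bias = correlation × [m(intervention share) − m(control share)], where m(q) = φ(Φ⁻¹(q)) / (1 − q) and m(0) = 0.

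| Excluded, intervention / control | Bias (SD) |
|---|---|
| 10% / 0% | 0.04 to 0.10 |
| 20% / 0% | 0.07 to 0.18 |
| 10% / 10% | 0 |
| 5% / 10% | −0.02 to −0.04 |

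The size depends on the assumed link between adherence and outcome, and the sign depends on which arm loses more people.

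**The case against.** The strongest reply is that the phrase is loose shorthand for people unable or unwilling to comply, judged at screening. It stands among entry conditions, and the statement that eligible people are then enrolled treats eligibility as settled beforehand. That may be what was meant, but the article does not say so, and four sites could apply the words differently. The need to reword stands either way.

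Three stronger readings are tempting, and the documents do not support them.

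- *A reader might infer that the rule is bound to favour the intervention arms.* Study procedures are not defined. They could mean visits, questionnaires and blood tests, and Table 1 schedules these without exempting controls. No exclusion rates by arm are given. Controls, who receive no structured intervention, could miss more visits, which would turn the bias the other way.
- *A reader might infer that the analysis cannot help because the records are deleted.* The article does not say that data already collected are discarded. If earlier records are kept, later values are missing, and maximum likelihood applies subject to its assumptions. It is equally true that nothing says the records are kept.
- *A reader might assume that 30% to 40% of one arm is removed, and so arrive at a much larger error.* That exceeds the 15% to 20% total attrition planned for, and non-adherers and dropouts probably overlap.

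The 13% also refers to a single unadjusted comparison, whereas the article plans a Holm-Bonferroni adjustment across the pairwise comparisons. It is an upper figure for the illustration, not a forecast.

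**Conclusion.** The point holds as a defect in a stated rule. As written, the criterion allows exclusion after allocation for behaviour closely related to the primary outcomes, and nothing else in the article neutralises it. Exclusion can differ by arm because the arms make different demands, so the comparison can be biased. Favouring the intervention arms is plausible, since they ask more of participants and the outcomes are behavioural, but it is not established.

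Under the simple illustration the false benefit is modest relative to d = 0.30 but enough to distort the error rate. The result rests on assumed exclusion shares, an assumed outcome gap, an equal split between arms and no exclusion of controls. The conclusion that the wording needs changing does not depend on those figures.

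**What to change.** 1. Delete the phrase from the exclusion criteria. Alternatively, restrict it to an inability or unwillingness to comply that is judged before enrolment and in the same way in all three arms.
2. State that everyone enrolled is followed up and kept in the primary analysis in the arm of their cluster, regardless of adherence or app use.
3. Record adherence as a process measure. Make any adherence-based analysis secondary.

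The cost is protocol wording. The estimated effect may be somewhat smaller, because less engaged people remain in the comparison. The Results section reports that only phase 1 data collection has been completed and that development of the digital intervention is still to follow, so on that account the change can be made before phase 3 recruitment.

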### Data Collection and Sampling Strategy

To ensure that each site implements all 3 arms while preserving feasibility and minimizing contamination, this study will use a clustered quasi-experimental design at the local community level.

#### Objective 1

To meet objective 1, both the quantitative and qualitative data will be collected. At each site, 8 focus group discussions will be conducted in community settings, with 8-10 individuals participating in each group. The in-depth interviews will be conducted with 10 individuals from the community and 10 community health workers. The Knowledge, Attitude, and Practice questionnaire, along with the other validated assessment tools, will be administered to 80 individuals from each site.

#### Objective 2

To meet objective 2, a total of 80 participants will be enrolled across 4 zones at each site to obtain their feedback on the developed digital platform.

#### Objective 3

To meet objective 3, participants at each site will be assigned to one of the following 3 study arms based on the site’s designated intervention:

Digital intervention arm: Participants will receive access to a mobile and web-based digital health platform developed by the Foundations of Healthcare Technologies Society, designed to promote NCD screening, health education, and behavior modification through interactive modules, personalized reminders, and self-tracking tools.WHO PEN arm: Participants will receive structured screening, counselling, and management services as per the WHO PEN protocols 1 and 2, implemented through trained health care providers and community health workers.Control arm: Participants will receive only routine health services available in their local setting, without any structured digital or WHO PEN-based intervention.

The sample size was determined to detect differences in primary outcomes (health-seeking behavior and NCD self-management) between the 3 arms. The initial sample size was adjusted for the cluster design, considering Cohen *d* as 0.30 for a small to moderate effect size, with 80% power and a significance level of 5%. Each study site will include 16 community clusters, resulting in a total of 64 clusters across the 4 sites. From each cluster, nearly 30 participants will be included with intracluster correlation coefficient of 0.02 and design effect of 1.58. The sample size will be adjusted for 15%-20% of attrition rate during the 12 months of follow-up period, resulting in the total sample size of 2400 (600 per site).

The comparative evaluation across these 3 groups will reveal differential effects on health-seeking behavior, self-management practices, and clinical outcomes. Figure 1 illustrates the study design framework, detailing the phases of data collection and intervention implementation. The summary of the quantitative data collection tools and outcome measures in the third phase of the study are described in Table 1.

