### Data Analysis Plan

Interviews and focus groups will be audio-recorded, transcribed verbatim, and translated to English where necessary. A thematic analysis approach will be applied using NVivo software (Lumivero). Triangulation across all the data sources will enhance validity. Data will be analyzed using SPSS (version 29; IBM Corp) and R software (R Foundation for Statistical Computing). Heuristic evaluation will involve the estimation of severity ratings, frequency of usability issues, time taken to complete tasks, and interrater reliability. Descriptive statistics will include means (SDs), medians (IQRs), and proportions to summarize baseline characteristics. Between interventions and control arms, the analysis would be performed by ANCOVA or generalized linear models, adjusting for baseline values, cluster effects, and site-level covariates. Statistical significance will be set at *P*<.05, with 95% CIs.

A generalized linear mixed-effects model will be used to conduct the primary analysis, because the data are clustered and longitudinal in nature. The generalized linear mixed-effects model will include random intercepts for the clusters of communities and the individual study participants to account for the intracluster correlation and repeated measurements over time. Intervention arm, time, and their interaction will be modelled as fixed effects, with study site included as a fixed effect to control for contextual differences. To control the baseline imbalance in outcome variable values, the baseline value will be used as a covariate in the analysis. The maximum likelihood estimation within the mixed-effects framework will handle the missing data in the study, with sensitivity analyses using multiple imputation. Pairwise comparisons among the 3 study arms will be conducted. This will be adjusted for multiple testing using the Holm-Bonferroni method, with statistical significance assessed at 2-tailed α level of .05.

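### The total of 2400 is clusters × 30 / 0.80 and does not come from d = 0.30 at 80% power; the error is conservative, but the stated power and detectable effect are not those of the design

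*Protocol article*

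**What the plan says.** All the inputs stand in one paragraph of the protocol article, under Data Collection and Sampling Strategy (Objective 3).

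- Effect, power and alpha: Cohen d of "0.30 for a small to moderate effect size, with 80% power and a significance level of 5" percent.
- Clusters: "Each study site will include 16 community clusters, resulting in a total of 64 clusters across the 4 sites".
- Cluster size and clustering: "From each cluster, nearly 30 participants will be included with intracluster correlation coefficient of 0.02 and design effect of 1.58".
- Total: after an allowance of 15%-20% for attrition, "resulting in the total sample size of 2400 (600 per site" in brackets.

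The paragraph shows no intermediate total and does not say whether 30 per cluster is counted before or after attrition.

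Two other sections bear on it. The Data Analysis Plan sets a two-tailed test and, for the pairwise comparisons of the three arms, says "This will be adjusted for multiple testing using the Holm-Bonferroni method". Study Design and Setting says "All eligible individuals within a cluster are enrolled into the arm designated for that cluster".

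**The concern.** The paragraph presents 2400 as the outcome of a power calculation. If the stated effect size and power do not generate that number, readers are misinformed on two points: the smallest difference the trial can reliably detect, and why this many people are asked to complete five assessment rounds with repeated laboratory tests. A null result would also be read against the wrong benchmark, 0.30 rather than about 0.20 to 0.23.

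A smaller matter is practical. If 30 is what remains after attrition, field teams must enrol more than 30 per cluster, and the article does not tell them so.

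**Working it through.** **Inputs.** From the sample-size paragraph: d = 0.30, power 80%, alpha 0.05, 64 clusters (16 per site), 30 per cluster, ICC 0.02, attrition 15%-20%. From the Data Analysis Plan: two-sided testing and Holm adjustment over three pairs, so the first step is 0.05/3 = 0.0167. Assumed here, because the article gives no ratio: equal arms. Power figures use the normal approximation.

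**1. The plan's own figures reproduce from the cluster count.**
- Design effect: 1 + (30 − 1) × 0.02 = 1.58, as stated.
- Total: 64 × 30 = 1,920, and 1,920 / 0.80 = 2400. Per site: 16 × 30 = 480, and 480 / 0.80 = 600.
- The 20% end of the attrition range was used; 15% would give 1,920 / 0.85 = 2,259.
- So 30 is the number left after attrition. Enrolment is 2400 / 64 = 37.5 per cluster.

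**2. The effect-size route does not reach 2400.**
- Per arm: n = 2 × (1.960 + 0.842)² / 0.30² = 174.4, rounded up to 175.
- × 1.58 gives 277 per arm; × 3 gives 831 analysed.
- 831 / 0.85 = 978 and 831 / 0.80 = 1,039 enrolled (973 and 1,033 without rounding at each step).
- At alpha 0.0167: 233 per arm, 369 after the design effect, 1,107 analysed, 1,303 to 1,384 enrolled.
- Other settings: alpha 0.05/6 with 80% power gives 1,602 enrolled at 20% attrition, and 2,029 with 90% power. Three-group ANOVA versions give about 800 to 1,275.
- The one variant that comes near is a change-score comparison with zero correlation between baseline and follow-up: 1,946 to 2,068 at alpha 0.05 and 2,359 to 2,506 at alpha 0.025. The article describes neither that alpha nor that analysis; it puts the baseline value in the model as a covariate.
- A separate 80% target in each site does not explain it either: 480 per site in three arms gives about 57%.

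**3. What the design delivers.** With 1,920 analysed there are 640 per arm, and 640 / 1.58 = 405 effective per arm. SE = √(2 × 1.58 / 640) = 0.0703.

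| | alpha 0.05 | alpha 0.0167 |
|---|---|---|
| Power at d = 0.30 | 99.0% | 97.0% |
| d detectable at 80% power | (1.960 + 0.842) × 0.0703 = 0.197 | (2.394 + 0.842) × 0.0703 = 0.227 |

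A t reference with 40 or 60 degrees of freedom in place of the normal changes the 99.0% only to about 98.6%-98.7%.

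**4. Sensitivity.**
- If teams enrolled only 30 per cluster: 1,920 × 0.80 = 1,536 analysed, 24 per cluster, design effect 1 + 23 × 0.02 = 1.46, 512 / 1.46 = 351 effective per arm. Power at d = 0.30 is about 98%, or 94% at 0.0167.
- If clusters split 5/5/6 at every site with the same arm always larger (20/20/24): comparing the two smaller arms, 600 analysed each, power is 98.5% and the detectable d at 0.0167 is 0.235 instead of 0.227.
- ICC at which 80% power for d = 0.30 would be true with 640 per arm: the design effect would be 640 / 174.4 = 3.67, so ICC = 2.67 / 29 = 0.092, against the stated 0.02.

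**The case against.** The strongest reply is that nothing is at risk. The paragraph gives its steps in order (clusters, about 30 each, attrition, total), the arithmetic of 2400 and of the design effect is right, and the trial has more power than it claims. A sponsor may want a margin for a higher ICC or heavier loss. All of that stands, and it limits the point to a correction of the justification. It does not rescue the statement itself: the article says the size was determined for d = 0.30 at 80% power, and it was not.

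Several stronger readings are tempting, and the article does not support them.

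- *1,920 contradicts 2400.* It does not; dividing by 0.80 reconciles them exactly. What remains is that the word for the 30 suggests enrolment when the arithmetic makes it completers.
- *A wrong power statement means an underpowered trial.* The error runs the other way, even if only 30 per cluster were enrolled.
- *Ignoring Holm in the sizing endangers the pairwise tests.* Power at the first step is still 97%, and sizing at that alpha would need at most 1,384.
- *Sixteen clusters cannot be divided among three arms.* The article never claims equal allocation, and an uneven split barely moves power.
- *The enrolment sentence in Study Design and Setting demands everyone in the ward.* It closes a passage on allocation and most naturally means that all participants in a cluster share its arm. It can be misread beside a fixed target, so it deserves clearer wording, but it is not a proven contradiction.

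**Conclusion.** The point holds in this form: 2400 is 64 × 30 / 0.80, while the stated effect, power and alpha justify about 975 to 1,040 enrolled, so the total is roughly 2.3 times what they call for (2400 / 1,039 = 2.3). The power and detectable effect as written are not those of the design. True power at d = 0.30 is about 99% (97% at the first Holm step), and 80% power corresponds to d of about 0.20 (0.23).

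This rests on about equal arms, 30 analysed per cluster and the stated ICC of 0.02. The ICC matters most, but it would have to be about 0.09 before the stated 80% became true. The error is conservative and does not affect the validity of the comparison.

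**What to change.** Keep 2400 and restate the sample-size paragraph.

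1. Give one of two statements, at the sponsor's choice, for 1,920 analysed in about equal arms: (a) power for d = 0.30 is about 97% at two-sided alpha 0.0167, the first Holm step (99% at 0.05); or (b) 80% power is reached for d of about 0.23 at 0.0167 (0.20 at 0.05). If (b) is used, call it the detectable effect, since it follows from the chosen size.
2. Say that 30 per cluster is the number analysed after 20% attrition, that 37 to 38 are enrolled per cluster, and that the design effect of 1.58 refers to the 30.
3. In Study Design and Setting, say that all participants enrolled from a cluster receive that cluster's arm, up to the enrolment target, so that the sentence cannot be read as a census of the ward.
4. Optionally, state the cluster split (for example 5/5/6 per site); it changes power very little.

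The cost is wording only: no more participants and no new sampling procedure. The Results section reports only phase 1 fieldwork as done and Table 2 places recruitment in phase III, so the text can apparently be corrected before enrolment starts.
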